#### Visit 6_TEL_ (postoperative day 30–35)

Visit 6_TEL_ is performed if the patient has been discharged before postoperative day 30–35. If the patient is still in hospital on day 30–35 visit 6_TEL_ is omitted. The visit should be conducted between day 30–35. This visit can be performed in person (outpatient clinic) or, if the patient cannot be seen in person, on the phone. The following data items have to be collected: a.) survival; b.) PRO-CTCAE symptoms; c.) CAT EORTC QLQ-C30; d.) reoperation(s); e.) (re-)hospitalization; f.) complication assessment according to the Clavien-Dindo classification; g.) SSI assessment according to the CDC classification; h.) details of postoperative oncological treatment; i.) weight.

#### Visit 7/8 (postoperative month 3/6)

Visit 7 and 8 have equivalent contents. Visit 7 and 8 can be performed in person (in person follow-up) or as a telecommunication visit (e.g. phone). The following data items need to be recorded: a.) survival; b.) PRO-CTCAE; c.) CAT EORTC QLQ-C30; d.) weight; e.) reoperation(s); f.) (re-)hospitalization; g.) oncologic treatment; h.) complication(s) according to the Clavien-Dindo classification.

#### Event Visit_1-x_ (anytime between visit 1–8)

Event visits are optional, i.e. they do not have to be performed but can be performed if necessary. The objective is to document survival, complications and/or PROs anytime during the study, i.e. between visit 1–8, if they are not covered by the other visits. The following data items should be collected: a.) date; b.) PRO-CTCAE; c.) CAT EORTC QLQ-C30; d.) survival; e.) reoperation(s); f.) hospitalization/readmission; g.) SSI assessment according to the CDC classification; h.) complication assessment according to the Clavien-Dindo classification; i.) oncological treatment; j.) weight.

### Risk-benefit assessment

As this is a non-interventional, observational study, no beneficial treatment effect is to be expected. Accordingly, no additional risk is expected for the individual participant. However, patients might benefit from more frequent and more thorough postoperative clinical visits by the local mini-teams. Furthermore, the study allows the patients to measure and feedback a number of PROMs which is not available for non-participating patients. During digital PROM evaluation patients have the opportunity to contact their local study team. Finally, the results of the study could benefit future patients by integrating and improving PROMs in the clinical treatment of cancer patients. Given the risk-benefit assessment no ancillary or post-trial care or compensation to those who suffer harm from the study is planned.

### Ethical and legal aspects, informed consent

The PATRONUS study will be conducted in agreement with the Declaration of Helsinki in its current version. This study protocol has been written and the study will be conducted and analysed in accordance with relevant national and international rules and regulations including international conference of harmonization good clinical practice (ICH-GCP) guidelines.

All patients will be informed of the aims and conduct of the study to allow an individual risk-benefit assessment based on informed consent. It will be emphasised that the participation is voluntary and that the patient is allowed to refuse further participation in the study whenever he/she wants to. In case of withdrawal from the study the patient will be asked whether her/his previously collected data may be used for analysis or not. In the latter case, all pseudonymised data entered in the eCRF will be deleted.

It is the responsibility of the investigator/medical student to maintain patients’ confidentiality. During the study, patients will be identified solely by means of their individual identification code. Study specific documents and patient data will be stored in accordance with local data protection law/ ICH-GCP Guidelines at the local trial sites and will be handled in strict confidence and in line with the obligations of medical secrecy, the EU General Data Protection Regulation (*Datenschutzgrundverordnung*), the Federal Data Protection Act (*Bundesdatenschutzgesetz*) and the State Data Protection Act (*Landesdatenschutzgesetz*). Participating patients’ data will be recorded in pseudonymised form.

The trial may be prematurely closed by the coordinating investigators in consultation with the responsible statistician and the steering committee. Reasons that may necessitate termination of the study include a.) it appears that patients’ enrolment is unsatisfactory with respect to quality and/or quantity or data recording is severely inaccurate and/or incomplete; b.) External evidence demanding a termination of the trial. The independent ethics committee (IEC) must then be informed.

The results of the trial will be published in a peer-reviewed journal under the authorship of CHIR-*Net* SIGMA. All participating personel will be listed with their specific contribution. Results will be distributed to the public via www.sigma.university, www.facebook.com/sigmastudynetwork and https://twitter.com/sigmastudies.

### Data management

An electronic case report form (eCRF) will be used for data collection. To assure a safe and secure environment for data acquired, the RedCap™ system (www.project-redcap.org) will be used for remote data entry [42]. RedCap™ is validated and compliant with FDA 21 CRF part 11. Data transmission is encrypted with secure socket layer (SSL) technology. The database server is located in a secure data centre at the University of Heidelberg, Germany and is protected by a firewall. The system provides an infrastructure to support user roles and rights. Only authorised users are able to enter or edit data, the access is restricted to data of the patients in the respective centre. All changes to data are logged with a computerized timestamp in an audit trail. All clinical data will be pseudonymized. Backups are conducted regularly.

All protocol-required information collected during the study will be entered by an authorised member of the mini-team in the eCRF. For HRQoL and PRO-CTCAE results, patients may directly enter the data in the eCRF. Any outstanding entries must be completed immediately after the final examination. An explanation should be given for all missing data. The completed eCRF must be reviewed and signed by an authorised member of the mini-team.

In order to guarantee quality, validity and plausibility of data, a data validation plan is implemented which uses real-time edit-checks and validating programs, which will generate queries. The investigator, medical student or the designated representatives are obliged to clarify the edit-checks and queries.

All data will be integrated in a statistical analysis system. The data access is restricted to the data manager and the biometricians responsible for the trial. The data will be managed and analysed in accordance with the appropriate Standard Operating Procedures valid in the Institute of Medical Biometry and Informatics at the University of Heidelberg.

A study-specific data validation plan has been established ensuring that implausibility of data, missing data and imbalances between centers, e.g. reporting of postoperative complications are revealed. In this case, queries will be sent to the centres and need to be resolved by the mini-teams. In the PATRONUS study only a limited on-site monitoring will be performed. An external monitor will check, whether signed informed-consent forms are available for all patients.

### Statistical procedures

Since this is an exploratory study, all analyses will be descriptive and *p*-values < 0.05 will be referred to as statistically significant in descriptive sense. The patient characteristics and outcomes will be described for the whole cohort and for the different subgroups divided according to tumour entity with appropriate descriptive statistics (mean, standard deviation, median, interquartile range, minimum, maximum in case of continuous data and scores, or absolute and relative frequencies in case of categorical data).

To analyse the association between perioperative complications (Clavien-Dindo grading) and the set of 12 PRO-CTCAE symptoms as well as the subscales of CAT EORTC QLQ-C30 in the short- and long-term, Spearman’s rank-correlation coefficients (Spearman’s rho) will be calculated and analysis of variance will be performed.

For the description of the absolute values of the CAT EORTC QLQ-C30 as well as the set of 12 cancer-specific symptoms measured via the PRO-CTCAE appropriate descriptive measures will be reported.

Possible overlapping between the two PROMs (PRO-CTCAE and CAT EORTC QLQ-C30) will be analysed calculating Spearman’s rhos between the respective scales.

The rates of missing PRO data, clinical data and the rate of included patients compared to screened patients will be calculated and reported with adequate descriptive measures. The number of participating trial sites including patients compared to initiated trial sites and the rate of included patients in comparison to screened patients per trial site will be calculated, as well. The achievement of the respective goal rates will be evaluated by binomial tests.

Further analysis includes correlations between ASA score, comorbidities, neoadjuvant therapy, socio-economic factors, smoking, alcohol consumption and other baseline factors and subscales of the two PROMs and complications. Survival analysis includes Kaplan-Meier graphs and log-rank-tests between different tumour entities. Cox regression analysis will be performed to evaluate possible relationships between survival and different baseline covariates.

Wherever appropriate, graphics will be created to illustrate the data and findings. Details of the statistical analysis will be described in the statistical analysis plan, which will be written prior to the database closure. For the statistical analysis, IBM SPSS Statistics Version 24 (or higher) and SAS (SAS Institute, Cary, NC, USA) version 9.4 (or higher) will be used. No interim analysis is planned.

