### Objectives

The primary aim of the study is to evaluate associations between the clinical outcomes and the two PROMs in the short-term (within 30 days) and long-term (after 3 and 6 months) in order to find out whether and to what extend complications (none/grade I vs. minor (grade II) vs. major (grade III-V)) influence the two PROMS in 5 predefined surgical cancer subgroups (upper-GI, pancreatic, hepatobiliary, colorectal, other abdominal cancers).

Further objectives are:To describe the absolute values of a.) the newly defined CAT EORTC QLQ-C30 and b.) the set of 12 cancer-specific symptoms [14] measured via the PRO-CTCAE [13] for oncologic patients undergoing surgery at predefined times from baseline (preoperative) until 6 months postoperative in the 5 surgical cancer subgroups outlined above.Although both of the proposed PROMs (PRO-CTCAE [13] and CAT version of the EORTC QLQ-C30) used in this trial have been validated, they are new and have never been tested head-to-head. Therefore, the existence of possible overlapping domains in both PROMs will be analysed.In order to find out if a student-led multicentre observational study using an electronic data capture system is feasible.

For the primary objective and further objective 1. and 2., the two PROMs (PRO-CTCAE and CAT version of the EORTC QLQ-C30) in the short-term (within 30 days) and long-term (after 3 and 6 months), as well as is the rate of postoperative complications grade II (minor) and III-V (major) within 30 days according to the Clavien-Dindo classification and the overall survival within 6 months postoperative will be assessed.

For further objective 3 the following endpoints will be assessed:Rate of missing PRO data at 3 and 6 monthsRate of missing clinical data at 30 daysNumber of participating trial sites including patients compared to initiated trial sitesRate of included patients in comparison to screened patients

Further endpoints can be found in the description of the study visits.

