### Patient timelines and description of study visits

Patients will be screened preoperatively (visit 1) by a member of the mini-team. Patients will be enrolled if they fulfil the inclusion/exclusion criteria and after having given their written informed consent after detailed patient information. Informed consent is sought by a member of the mini-team, i.e. medical student or clinical trialist (surgeon). Baseline data and the first set of PROMs are collected during screening/baseline visit. Surgical data is collected during visit 2. Short-term clinical outcome parameters and PROMs are collected during visits 3–6 within 30 postoperative days or until discharge. Long-term clinical data and PROMs are collected at visit 7 and 8. Detailed information about the collected data during the patients’ visits is displayed in Table 2 (SPIRIT figure).

**Table 2 Tab2:** Adapted SPIRIT figure showing the visits and documented parameters of the PATRONUS study

Activity	Visit 1 (screening, consent)	Visit 2 (surgery)	Visit 3–6 (POD 3–5, 6–8, 10–14, 30–35 or at discharge)	Visit 6_TEL_ (POD 30–35 if patient has been discharged before)	Visit 7/8 (postoperative month 3 and 6)
expenditure of time per visit approx	20–25 min	–	15 min	15 min	15 min
Inclusion/exclusion criteria	X				
Informed consent	X				
Demographics and baseline data	X				
Documentation of PROMs: a.) 12 symptoms PRO-CTCAE* b.) cancer-specific HRQoL**	X		X^§^	X	X
Surgery		X			
Postoperative morbidity***			X	X	
SSI^$^			X	X	
Length of hospital stay			X	X	X
Reoperations			X	X	X
(Re)admissions			X	X	X
Overall survival			X	X	X

* 12 symptoms as recommended by the National Cancer Institute: fatigue, insomnia, pain, anorexia, dyspnoea, cognitive problems, anxiety, nausea, depression, neuropathy, constipation, diarrhoea assessed via PRO-CTCAE™

** according to the EORTC quality of life questionnaire C30

*** according to Clavien-Dindo

^$^ Documentation of SSI according to CDC [40, 41]

^§^ HRQoL once only on POD 30–35 or at discharge (Visit 6)

TEL Visit can be performed by telephone

*SSI* surgical site infection, *CDC* Centers of Disease Control and Prevention, *POD* postoperative day, *OS* overall survival, *PROM* patient-reported outcome measure, *CTCAE* Common Terminology Criteria of Adverse Events, *HRQoL* health-related quality of life

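### The methods named for the primary complication–PROM association give no role to the preoperative PROM score or the other baseline factors already collected

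*Protocol article*

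**What the plan says.** Objectives opens the primary aim as an evaluation of associations between the clinical outcomes and the two PROMs. It then gives the purpose as finding out "whether and to what extend complications (none/grade I vs. minor (grade II) vs. major (grade III-V)) influence the two PROMS", and sets this "in 5 predefined surgical cancer subgroups (upper-GI, pancreatic, hepatobiliary, colorectal, other abdominal cancers".

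For the link between Clavien-Dindo grade and the PROM scales, Statistical procedures names two methods: "Spearman’s rank-correlation coefficients (Spearman’s rho) will be calculated and analysis of variance will be performed". No covariate, baseline score or centre term is mentioned.

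Baseline factors appear later in the same section, as "correlations between ASA score, comorbidities, neoadjuvant therapy, socio-economic factors, smoking, alcohol consumption and other baseline factors and subscales of the two PROMs and complications". The one regression model named is Cox regression, and it concerns survival.

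The preoperative scores exist: "Baseline data and the first set of PROMs are collected during screening/baseline visit". The list for Visit 1 includes both instruments.

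Statistical procedures calls all analyses descriptive and leaves details to a statistical analysis plan, which is not shown. The Discussion states as its first limitation that the design cannot establish causation. Missing values rules out imputation.

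**The concern.** Complications are not assigned at random. A patient who enters surgery with poor function, a higher ASA grade or more comorbidity may be more likely both to have a complication and to report worse scores afterwards. If post-operative scores are compared across grades without reference to the starting point, that patient counts as evidence about complications.

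The protocol itself lists the candidates. It plans to correlate ASA, comorbidities, neoadjuvant therapy and other baseline factors with the PROMs and with complications. A preoperative variable related to both is a candidate confounder, but separate correlations adjust nothing. Ordinary Spearman's rho cannot adjust for anything either.

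Two things are at stake. The answer to the question of extent may be too large, and it will be less precise than the collected data allow. The Discussion also expects the data to support sample size calculation for future trials, so an inflated difference would be carried into them.

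**Working it through.** **Plan's own figure.** Sample size calculation gives 30 clinics × about 30 evaluable patients = 900. This reproduces. The document gives no effect size, SD, complication rate or correlation, so every other input below is an assumption.

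**Assumed inputs.** Complication shares are 60/20/20% for none or grade I / grade II / grade III-V. The correlation of baseline with follow-up PROM is r. The correlation of baseline PROM with latent complication severity is a. Higher values mean worse on both scales. The true effect of complications is zero. Tests are two-sided at 0.05, with 1,000 runs per scenario.

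**Expected spurious difference, major vs none/grade I.** With severity cut at the 60th and 80th centiles of a standard normal, the mean severity is
- top 20%: φ(0.8416)/0.20 = 0.2800/0.20 = 1.400
- bottom 60%: −φ(0.2533)/0.60 = −0.3863/0.60 = −0.644

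The gap is 2.044, so the spurious difference in SD units is r × a × 2.044.

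With r = 0.5 and n = 900:

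| a | Formula (SD) | Simulated (SD) | Mean rho | Spearman p<0.05 | One-way ANOVA p<0.05 | ANCOVA p<0.05 | ANCOVA difference (SD) |
|---|---|---|---|---|---|---|---|
| 0 | 0 | 0.00 | 0.00 | 5% | 5% | 5% | 0.00 |
| 0.1 | 0.102 | 0.103 | 0.04 | 23% | 21% | 4% | 0.00 |
| 0.2 | 0.204 | 0.208 | 0.08 | 69% | 63% | 6% | 0.00 |
| 0.3 | 0.307 | 0.305 | 0.12 | 95% | 93% | 6% | 0.00 |

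The ANCOVA adjusts for baseline PROM and tumour site.

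**A second set of assumptions.** Take 17–18% major complications, r = 0.5, and odds of a major complication multiplied by 1.35 or 1.65 per SD worse baseline. Simulated crude differences are 0.15 and 0.24 SD in the worse direction. The approximation r × ln(OR) gives 0.5 × 0.300 = 0.15 and 0.5 × 0.501 = 0.25. The order of magnitude agrees.

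**Tumour site.** Let site act on both severity and PROM with path 0.3, and set a = 0. The pooled difference is 0.3 × 0.3 × 2.044 = 0.184 SD (simulated 0.185). With site as a factor it is about 0. With a = 0.2 added, site adjustment alone still leaves 0.22 SD, which comes from the baseline score.

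**Within a subgroup.** Assuming equal fifths, 900/5 = 180 patients. For a = 0.1 to 0.3 the spurious difference is 0.11 to 0.31 SD, the same size as before. It reaches p<0.05 less often: Spearman 9–38%, ANOVA 7–33%. Stratifying by tumour site does not remove confounding by baseline score.

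**Precision.** Adjusting for a baseline with correlation r removes about r² of the residual variance, equivalent to multiplying the sample by 1/(1 − r²). For r = 0.4 this is 16% and 1.19; for r = 0.6 it is 36% and 1.56. Correlation between baseline and complication grade takes back a little of this gain.

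**The case against.** **The analysis plan may already cover this.** Analysis of variance can carry further factors, the protocol does not say one-way, and it defers details. A reader might infer that the sponsor has committed to a crude comparison. The text does not support that; it supports only that no adjustment is named. What remains is that the published method, followed as written, gives the preoperative score no role, while covariates are named for the survival analysis.

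**The study claims no causation.** This is largely right. Objectives speaks of associations, Statistical procedures treats significance descriptively, and the Discussion disclaims causality. A reader might infer that results will be presented as effects of complications, but the document does not say so. The verb in the aim, and the similar one in the abstract, invite that reading without requiring it. A disclaimer also does not remove bias that measured variables could reduce.

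**The rejection rates are not false positives for an association.** This stands. In the simulation a marginal association really exists, so a test of association is right to detect it. The rates become misleading only if the result is taken as the contribution of the complication itself.

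**Tumour site is handled.** Mostly so. The aim is set within five subgroups, so site mix confounds only a pooled result. Sample size calculation does promise answers overall as well as by subgroup, and the association analysis is not explicitly stratified.

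**Centre differences are handled.** Partly. Data management plans checks for between-centre imbalance in complication reporting, and the Discussion describes Clavien-Dindo training for the students. These address data quality; they do not put centre into the analysis.

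**Conclusion.** The point holds in a limited form. The aim asks how far complications influence the PROMs, and the methods named for it state no adjustment for the patient's preoperative state, although the necessary data are collected. Differences between grades may therefore partly reflect that state, in pooled and subgroup results alike.

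The size in this cohort is unknown. The figure of roughly 0.1 to 0.3 SD depends wholly on assumed values (a of 0.1 to 0.3, r of 0.5, shares of 60/20/20%) and on a true effect of zero. It scales with r × a and vanishes if baseline score and complication risk are unrelated. The document gives none of these quantities.

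A reader might take this for a must-fix error. The declared exploratory and descriptive status, the causal disclaimer and the deferral to an analysis plan do not support that. It is a recommended improvement at low cost.

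**What to change.** Specify in the statistical analysis plan, before database closure:

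- **Main estimate.** For each PROM domain, the adjusted difference for grade II vs none/grade I and for grade III-V vs none/grade I, with 95% CI.
- **Model.** ANCOVA, or an ordinal or mixed model where the scale or repeated visits call for it. Include the baseline value of the same domain, age, ASA/comorbidity, neoadjuvant therapy and centre, plus surgical category for pooled results.
- **Excluded covariates.** Nothing that follows the complication, such as length of stay or reoperation.
- **Descriptive supplements.** Keep Spearman's rho and the unadjusted analysis of variance, labelled as unadjusted.
- **Wording.** State the aim and conclusions as (adjusted) association, in line with the limitation in the Discussion.

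The cost is some analysis-plan text and a little programming; no new data are needed. The one real downside is that Missing values rules out imputation, so patients without a baseline PROM drop out of the adjusted model. Report their number, and show the unadjusted result beside the adjusted one so that the effect of losing them can be judged. Adjustment covers measured factors only, so the causal disclaimer should stay.

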### Study conduct and study centres

To enrol an adequate number of patients in the planned recruitment period, 30 hospitals including regional centres of the clinical trial network CHIR-*Net* (www.chir-net.de/regionalzentren-karte) as well as associated partner-hospitals will participate in the study.

A CHIR-*Net* SIGMA steering group for the PATRONUS study has been set up consisting of the authors of this publication and include the CHIR-*Net* coordination centre. This steering group has designed the study and is responsible for trial infrastructure, acquisition of centres, qualification of participating medical students and communication with centres and the public via digital tools (www.slack.com) and social media (www.facebook.com/sigmastudynetwork; https://twitter.com/sigmastudies).

At each trial site a so-called “mini-team” will be established consisting of an experienced clinical trialist (surgeon) and a group of at least two medical students. Furthermore, at each site a “local lead” will be appointed. The local lead is a medical student responsible for creating the mini-team, recruiting other students to the project, interacting with local surgeons and conducting the study. The local lead in conjunction with the associated surgeon is also responsible for gaining approval for the study from his/her local independent ethics committee according to the German Medical Association’s professional code (*Berufsordnung der Bundesärztekammer*).

All student participants will be trained prior to study initiation. To this end CHIR-*Net* SIGMA has developed an in-person and online clinical trials training programme (SIGMA clinical trial curriculum; SIGMA-CTC) which will be reported elsewhere.

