### Eligibility criteria

Every local team will recruit patients for the study independently. Inclusion criteria are: a.) patient’s age ≥ 18 years; b.) patient scheduled for elective abdominal surgery for confirmed or suspected malignancy; c.) patient’s ability to understand character of the study; d.) planned laparoscopic or open surgery or any variant (i.e. laparoscopic-assisted, laparoscopic-thoracoscopic), e.) written informed consent. Exclusion criteria are a.) language barrier that impedes follow-up or informed consent, b.) American Society of Anesthesiologists (ASA) grade ≥ 4.

All patients planned for an elective surgery for suspected or confirmed malignancy are asked for their participation in the trial if all inclusion criteria and none of the exclusion criteria are fulfilled. Screening lists are kept in order to analyse reasons for non-inclusion of patients and to calculate the case ascertainment rate.

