### Sample size calculation

Since this is an exploratory cohort study, no formal sample size calculation was done. Assuming 30 clinics to participate and a recruiting rate of about evaluable 30 patients per centre, we assume to have the data of about 900 patients to evaluate. This sample size is big enough to give answers with a good precision overall and in specific subgroups such as different cancer entities.

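### The binomial tests of the patient-level feasibility rates ignore clustering by the roughly 30 student teams, so they overstate certainty in either direction

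*Protocol article*

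**What the plan says.** Further objective 3 (Objectives) asks whether a student-led multicentre study with electronic data capture is feasible. It has four endpoints: missing PRO data at 3 and 6 months, missing clinical data at 30 days, sites that include patients relative to sites initiated, and included relative to screened patients.

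Statistical procedures reports these descriptively, adds the inclusion rate per site, and then states: "The achievement of the respective goal rates will be evaluated by binomial tests". No allowance for site is mentioned. Of p-values the same section says: "values < 0.05 will be referred to as statistically significant in descriptive sense".

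On structure, Study conduct and study centres plans for "30 hospitals including regional centres of the clinical trial network", each with its own mini-team and student local lead. Eligibility criteria adds: "Every local team will recruit patients for the study independently". Under Data management, mini-team members enter the data and resolve queries, and patients may enter PRO answers themselves. Sample size calculation assumes "a recruiting rate of about evaluable 30 patients per centre".

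On withdrawal, Ethical and legal aspects has the patient asked whether data already collected may be used. If the patient refuses: "In the latter case, all pseudonymised data entered in the eCRF will be deleted".

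**The concern.** A binomial test takes each patient as an independent trial with one common probability. Whether a patient is included, reached at 3 or 6 months, or fully documented at 30 days depends partly on the local team: its size, diligence and access to the ward. Patients of one team therefore tend to succeed or fail together. The pooled rate then varies more than the binomial formula allows, and a chance departure from the goal is too readily called real.

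This bears on the objective itself, because team performance is what further objective 3 examines. The inclusion rate per site shows the spread between teams but does not correct the pooled test.

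A second, conditional issue concerns the denominator. If the missing-data rate is computed from the eCRF alone, a patient whose record has been deleted leaves both numerator and denominator, although that patient is a loss.

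**Working it through.** **Inputs from the article.** 30 sites; about 30 evaluable patients per site; nominal level 0.05.

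**Inputs not in the article, assumed.** ICC by site 0.02, 0.05 or 0.10; a goal of 80% data completeness, where a goal is needed; a two-sided test unless stated, since sidedness is not given; the share of patients deleted after withdrawal.

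**The article's own figure.** 30 × 30 = 900, as stated. No power or error rate is given for the binomial tests, so there is nothing further to reproduce.

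**Clustering.**
- Design effect: DE = 1 + (30 − 1) × ICC.
- Effective sample size: 900 / DE.
- Type I error of a nominal 5% two-sided test: 2 × [1 − Φ(1.96 / √DE)].
- 95% half-width at 80%: 1.96 × √(0.8 × 0.2 / 900) = 2.6 points under independence, multiplied by √DE.

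| Assumed ICC | DE | Effective n | True type I error | Half-width at 80% |
|---|---|---|---|---|
| 0 | 1.00 | 900 | 5% | 2.6 points |
| 0.02 | 1.58 | 570 | 12% | 3.3 points |
| 0.05 | 2.45 | 367 | 21% | 4.1 points |
| 0.10 | 3.90 | 231 | 32% | 5.2 points |

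A beta-binomial simulation of the exact test (30 sites of 30, goal 80%, 100,000 runs) agrees. The two-sided error is 11.2%, 20.2% and 31.1%. The one-sided error is 8.4%, 13.8% and 19.6%, against about 4.2% under independence. Even at an ICC of 0.01 the two-sided error is 7.7%.

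**Direction.** By the normal approximation the two-sided error splits evenly between tails. The chance of wrongly declaring the goal exceeded is about 6%, 11% and 16%, against a nominal 2.5%, and the chance of wrongly declaring it missed is the same.

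**Scope.** The cluster size of 30 is evaluable patients, so the table applies to the missing-data rates. For included versus screened, the cluster is the site's screened patients, whose number is not given; the problem is the same in kind but is not sized here. For sites including patients over initiated sites, the site is the unit and no clustering correction is needed.

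**Deletion after withdrawal.** Let d be the share of enrolled patients deleted, all of them true losses. The apparent missing rate is (true rate − d) / (1 − d). With a true rate of 20%:
- d = 1%: (0.20 − 0.01) / 0.99 = 19.2%.
- d = 5%: (0.20 − 0.05) / 0.95 = 15.8%.

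The bias is zero if nobody refuses use of the data, or if deleted patients are counted from other records.

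**The case against.** The strongest reply is that little hangs on these tests. All analyses are declared exploratory and descriptive, feasibility is the last of the further objectives, no go/no-go rule depends on it, and the inclusion rate is also shown per site. The ICC is an assumption throughout. This stands as a reason for low severity. It does not rescue the test: the article still attaches significance to reaching the goals, and a descriptive p-value or interval is wrong if its independence assumption fails.

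A reader might go further in four ways that the documents do not support.

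- **That the feasibility result will look too favourable.** Clustering errs in both directions. A favourable bias could come only through deletion, which needs both withdrawal and refusal of data use. Its frequency is not given, and no passage says that such patients leave the denominator. Screening lists and signed consent forms exist outside the eCRF.
- **That the goal rates are missing or were set late.** "The achievement of the respective goal rates" presupposes goals set somewhere. A journal article may leave their values to the full protocol or the analysis plan, and it says so of analysis detail in general: "Details of the statistical analysis will be described in the statistical analysis plan, which will be written prior to the database closure". Nothing shows that the goals were chosen after the rates were seen.
- **That deaths are confused with non-response in the study's favour.** Survival is recorded at every postoperative visit, so deaths can be separated. Counting them as missing would raise the missing rate, not lower it.
- **That all four tests are affected.** The site-level endpoint is not.

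**Conclusion.** The point holds for the patient-level feasibility rates. The article fixes a simple binomial test, and its own description of separate local teams contradicts the independence which that test requires. Under any positive site ICC the tests, and any binomial intervals, are too certain in either direction. At assumed ICCs of 0.02 to 0.10 with 30 sites of 30, a nominal 5% two-sided test runs at about 12% to 32%.

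The figures rest on an assumed ICC and equal site sizes, and on treating the sites as a sample of teams that could run such a study, which is how the objective reads. The remark on deletion is conditional: it matters only if such patients occur and are not counted. Severity is minor.

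**What to change.** - For missing PRO data, missing clinical data and included versus screened, replace the simple binomial test by a site-clustered estimate with a 95% confidence interval, compared with the goal rate. Cluster-robust, GEE or beta-binomial methods all serve; with about 30 clusters, use a small-sample correction for the first two.
- Keep the exact binomial test for sites including patients over initiated sites.
- For the missing-data rates, count patients whose eCRF data were deleted after withdrawal as missing, taking their number (not their data) from the consent or screening records.

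The cost is a few sentences in the analysis plan, wider intervals and possibly a slightly higher reported missing rate. No new data are needed.
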